#### **Serious Adverse Event (SAE)**

An SAE is defined as any AE that:

- results in death; or
- is immediately life threatening; or
- requires inpatient hospitalisation; or
- requires prolongation of existing hospitalisation; or
- results in persistent or significant disability/incapacity; or
- is a congenital anomaly/birth defect.

Important medical events will be considered an SAE when, based upon appropriate medical judgement, they may jeopardize the patient and may require medical or surgical intervention to prevent one of the outcomes listed in this definition.

We recognise that participation in the right@home study may be a cause of potential stress or harm to participants, if it asks questions that are distressing, or if participation leads to disagreements or fights between the participant and her partner and/or family. Potential stress will be minimised in the following ways:

1. The participant will be fully aware of the reason for the questions asked in the assessments
2. The participant will be advised that they can decline to continue in the trial at any time
3. Participants will be offered appropriate referral for any concerns raised

At recruitment screening, any women who becomes distressed will be encouraged to discuss their concerns with the health provider they are about to see. During the study if a research assistant is

concerned about a parent they will discuss this with the PI. With the parent's permission a referral mechanism will be in place to the parent's local doctor or maternal and child health nurse. This process has been implemented successfully with a number of other studies that specifically ask about self harm behaviour. If the parent is within the intervention arm the PI will contact the parent and ask permission to refer back to the intervention nurse.

At the 6 week, 6 month and 18 month follow-up phone assessments, women will be asked what things they like and dislike about being part of the study, and whether being part of the study has caused them any harm so far. These questions will be developed based on previous MCRI studies that have successfully used these processes (e.g. Weave Study, Healthy Mothers Study) and submitted for approval in a future ethics modification.

Participants will be advised that non-participation in the trial will not affect their access to routine antenatal, postnatal and early childhood clinical management and services. Participants will, at a minimum, receive usual clinical management in accordance with Victorian and Tasmanian universal antenatal, postnatal and child and family management protocols. Participation in the research will not adversely affect the participants – it is hypothesised that participants in the intervention group will show improved child and maternal outcomes.

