## **6.8 Continuation of Therapy**

The home visiting intervention will not be offered to participants beyond the child's second birthday.

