## **7. STUDY VISITS AND PROCEDURES SCHEDULE**

The Study diagram in Section 4.2 and Figure 3 below depict the study visits schedule. From April 2013 to March 2014, researchers will approach women at antenatal clinics listed in Section 1.1 to invite women to take part in the screening survey (**Appendix 15**). At this point, consent involves agreeing to complete the screening survey and, if eligible, being invited into the right@home trial. Researchers will then visit interested and eligible women in their homes within 1-2 weeks of the initial screening procedure, to tell them more about the right@home study, and collect informed consent for participation in the randomised controlled trial and a thorough baseline assessment.

Once women complete the baseline assessment, they will be randomised into one of the intervention or usual care arms. Whether this randomisation takes place in the woman's home (at the end of the enrolment visit) or over the phone will depend on whether the intended electronic data collection processes can incorporate the web-based randomisation program, and whether the tablets can connect via 3G/wireless internet. Once a woman is randomised, her details will be sent to the right@home nurse coordinator responsible for that region, and the nurse will be responsible for initiating contact and beginning the intervention. Follow-up assessments will be conducted by the research team via phone at 6 weeks, 6 months and 18 months postpartum, and via face-to-face home visits at 12 and (the final follow-up at) 24 months.

Due to the anticipated low literacy level of the participant group, we are designing all assessments so that they can be completed face-to-face by interview. Responses will be recorded by researchers electronically on tablets, except for some sensitive questions (highlighted in the questionnaire), where the participant will be given the option to complete by themselves either by reading it or having it read to them.

**Figure 5: Graphical depiction ('Perera diagram') of the components of the trial shared and unique to the intervention and control groups**

| Time point relative to randomisation                | Intervention                                                                                                             | Control |

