## 8. CLINICAL ASSESSMENTS

We plan to collect all assessment data electronically via tablets; however, we will print paper versions of all assessments as backup for possible electronic malfunctions.

**Screening:** The purpose of this face-to-face assessment is to identify eligible women and invite them into the right@home trial. As described in Section 6.1, researchers will approach pregnant women in antenatal clinic waiting rooms using the script in **Appendix 16**. Interested women will be asked to complete informed consent (see **Appendix 17**) and complete the screening survey (see **Appendix 15**), either with the researcher or alone. Using the eligibility algorithm identified by the pilot (RCH HREC # 32271, Northern Health HREC P 20/12), researchers will identify eligible women from their survey responses and invite them into the next phase of the trial. This involves describing RCT participation, giving women the information statement for participation in the randomised controlled trial (**Appendix 2**), recording their contact details and organising a time to visit them in their home to conduct the formal enrolment.

**Baseline enrolment:** The purpose of this face-to-face assessment is to formally enrol (i.e. obtain informed consent) for participation in the right@home trial, and conduct a comprehensive baseline assessment of women. A researcher will visit the participant in her home (or at The Royal Children's Hospital or a mutually-convenient location nearby, depending on the woman's preference and researcher safety). The researcher will answer any questions the woman has about the Information Statement given to her at the screening assessment and collect informed consent (see **Appendix 17**). The researcher will then conduct the baseline questionnaire with the mother (see **Appendix 20**). The questionnaire will be collected in a private space, i.e. a separate room with only the mother, the researcher, and any young children that the mother needs to care for, present. The baseline assessment includes the mother completing the SDQ for any children aged 3-6 years (see Sections 4.5 and 7 above). We expect the baseline enrolment assessment will take 50-60 minutes to

complete face-to-face, based on purposeful piloting (i.e. the interviewing was undertaken with the understanding that it would be a slower process than anticipated) with our research staff.

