### **9.3 Eliciting Adverse Event Information**

Adverse events will be recorded from the time the patient signs the informed consent form until 30 days after the last intervention nurse visit. At every study visit patients will be asked “How have you felt since your last visit?” in order to elicit any medically related changes in their well-being. They will also be asked if they have been hospitalised, had any accidents, used any new medication or changed concomitant medication regimens. In addition, AEs will be documented from physical examination findings, clinically significant lab results or other documents (including patient diaries and correspondence from their primary care physician) that are relevant to patient safety.

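### The question whether taking part has caused harm is last put at 18 months, although the programme and follow-up run to 24 months, and the general adverse-event question fills that gap only in part

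*Protocol*

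**What the plan says.** Section 9.1 of the protocol, under the serious adverse event heading, accepts that taking part may itself do harm. It names two routes: questions that upset the woman, and trouble at home, "if participation leads to disagreements or fights between the participant and her partner and/or family". It then sets out how such harm is to be asked about: "At the 6 week, 6 month and 18 month follow-up phone assessments, women will be asked what things they like and dislike" about being in the study, and "whether being part of the study has caused them any harm so far". It adds that these questions are still to be developed and will go to the ethics committee in a later modification.

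Section 7 gives the contact schedule. Three contacts are calls: "Follow-up assessments will be conducted by the research team via phone at 6 weeks, 6 months and 18 months postpartum". The other two take place in person, the second of them closing the trial's follow-up: "via face-to-face home visits at 12 and (the final follow-up at) 24 months". Section 6.8 fixes the end of the programme: "The home visiting intervention will not be offered to participants beyond the child's second birthday".

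Section 9.3 adds a general adverse-event question. It is put at every study visit, "in order to elicit any medically related changes in their well-being", and is followed by prompts on hospital stays, accidents and medication. Recording runs from consent to 30 days after the last visit by the intervention nurse. Section 9.2 has each event graded for its relation to the study treatment.

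**The concern.** The protocol foresees harm from participation and plans a question aimed at it, but the schedule for that question stops six months before exposure does. Nurse visits continue after the 18-month call, and the 24-month home assessment brings a further set of sensitive items. A woman whose distress or family conflict began after 18 months, and who puts it down to the study, has no scheduled occasion on which she is asked about that link.

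At stake are participant protection and the completeness of any statement on harms. Section 9.1 also says that participation will not adversely affect women. Support for that statement would need the question to cover the whole period of exposure.

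**Working it through.** No sample size, power or event rate underlies this point, so there is no figure of the plan to reproduce. The check sets the schedules side by side.

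Inputs: timing of the harm item (Section 9.1); contact schedule and mode (Section 7); end of programme (Section 6.8); general adverse-event question (Section 9.3); the social support and sensitive-issues rows of Table 4; nurse-visit frequency (Section 5.1.1).

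| Contact | Mode | Participation-harm item | General adverse-event question | Social support and sensitive-issues rows |
|---|---|---|---|---|
| 6 weeks | phone | yes | if a call counts as a study visit | no |
| 6 months | phone | yes | if a call counts as a study visit | no |
| 12 months | home | no | yes | yes |
| 18 months | phone | yes | if a call counts as a study visit | no |
| 24 months | home | no | yes | yes |

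Step 1, interval after the last asking: 24 − 18 = 6 months. As a share of the postnatal period this is 6 / 24 = 25%. As a share of the 2½-year programme (30 months) it is 6 / 30 = 20%.

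Step 2, exposure in that interval: Section 5.1.1 sets bi-monthly nurse visits up to 2 years. Read as one visit every two months, which fits the tapering schedule, this gives 6 / 2 = 3 visits per family. With 400 intervention families all attending, it is 3 × 400 = 1,200 visits. That total describes scheduled contact under full attendance. It is not a count of missed harm, for which the protocol gives no rate.

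Step 3, the 12-month visit: the harm item asks about the study so far, so it is cumulative. The 18-month call therefore reaches back over the 12-month home assessment. The uncovered stretch is months 18 to 24 only.

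Step 4, what Section 9.3 supplies at 24 months: the 24-month home assessment is a study visit on any reading, so the general question and its prompts apply there and look back to the previous visit. Their stated aim is medical, and Section 9.1 defines an adverse event in medical terms. A woman may mention distress or conflict in reply to an open question about how she has felt, but nothing asks her whether the study was the cause.

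Step 5, after the final visit: no later contact is scheduled. Only the 30-day recording window remains. It is tied to the last intervention-nurse visit, which control women do not have.

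**The case against.** The strongest reply is that the protocol's adverse-event system as a whole already covers the last six months:

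- Section 9.3 asks an open question about well-being at every study visit, including 24 months.
- Section 9.2 says that the events most likely to be met are psychosocial, substance-related, or matters of home safety and child protection, and it has each event graded for relatedness.
- Table 2 lists a family psychosocial instrument that covers domestic violence. The Table 4 rows it most naturally belongs to are marked at enrolment, 1 year and 2 years, all face to face. The row names differ from the instrument's name, so this match is an inference.
- Maternal mental health is measured at 2 years.
- A research assistant worried about a parent can raise it with the principal investigator at any time.
- Section 10.1 gives a reason for collecting data by phone: to lighten the home assessments.

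Most of this stands, and it limits the point. A reader might infer from Section 9.1 alone that harm after 18 months is never asked about, or that harm data stop at 18 months. Section 9.3 rules out both. A reader might also infer that partner conflict is asked about only by phone, where no private setting is laid down. The Table 4 rows point the other way, and Section 7 lets women complete some sensitive questions themselves. What is confined to the phone is whether participation caused the conflict. Section 8 does specify privacy for the baseline interview ("The questionnaire will be collected in a private space, i.e. a separate room with only the mother, the researcher, and any young children"), but it describes only screening and baseline, so its silence on later contacts is not evidence of an unsuitable setting. Nor do the documents show a bias towards finding no harm. Incomplete ascertainment is as far as they go.

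The reply does not supply the missing attribution. Relatedness grading in Section 9.2 works only on events that have already come to light. The domestic-violence and mental-health measures record a state, not whether the study brought it about. The protocol evidently saw a need for a separate question on this, since it planned one.

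**Conclusion.** The point holds in a narrow form. The participation-specific harm item is scheduled at 6 weeks, 6 months and 18 months and not at 24 months. The last 6 of 24 postnatal months therefore have only a medically directed general question, which covers study-related distress or family conflict in part. How many harms would be missed cannot be estimated from the document.

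The conclusion assumes that Section 9.1 gives the full schedule of the item (Table 4 has no row for it) and that the 24-month home assessment counts as a study visit under Section 9.3. It is a worthwhile, inexpensive improvement to harm ascertainment. It has no bearing on the primary comparison.

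**What to change.** In Section 9.1, extend the schedule of the harm item to the 24-month home assessment, for both arms. Put it at the end of that interview, so that distress from the interview itself can be mentioned. Ask it in private, as at baseline, or by the self-completion option that Section 7 offers for sensitive questions. Keep the cumulative wording, so that a woman who missed the 18-month call is also covered. Add a row to Table 4 showing every time the item is asked. Asking it at 12 months as well is optional, because the 18-month call already looks back over that visit.

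The cost is a few minutes of interview time at 24 months. The item still has to go to the ethics committee, so the extra time point can travel in the same submission. One limit remains: a question asked at the final visit cannot pick up harm that arises after it.

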## **4. STUDY DESIGN**

### **4.1 Type of Study**

This is a longitudinal, randomised controlled, multi-site evaluation of a sustained nurse home visiting program compared with usual care. The program will be offered to families from the antenatal period to the final follow-up assessment at child age 2 years. Researchers responsible for collecting the data, but not families or nurses, will be blinded to participating families' randomisation status.

A critical feature of the current trial is that it is designed based on strict program logic (see Figure 2 below), which is lacking in many of the previous home visiting randomised trials. A recent review by Segal et al (2012) of home visiting programs to reduce child maltreatment showed that programs based on strict program logic were much more likely to be effective than those that were not. As such, we are designing the trial to ensure any effects can be clearly traced back to the intervention offered. Specifically, the right@home intervention is based on the MECSH SNHV program, but is being enhanced to include evidence-based strategies on three focus modules which specifically target the three primary outcomes measured at age 2 years: parent care and responsivity, and a supportive home learning environment.

Figure 2: Program logic for the right@home trial

[figure not shown]

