| Measure                                                                                                                  | Description                                                                                                                                                                                                                                   |
|--------------------------------------------------------------------------------------------------------------------------|-----------------------------------------------------------------------------------------------------------------------------------------------------------------------------------------------------------------------------------------------|
| 2. Parent responsivity:                                                                                                  |                                                                                                                                                                                                                                               |
| Parent responsivity subscale (observational) of the Home Observation for Measurement of the Environment Inventory (HOME) | Quality and quantity of stimulation and support available to a child in the home environment. Assessed through observation and interview with the primary caregiver (usually the mother) of the child in the family home.                     |
| 3. Home Environment:                                                                                                     |                                                                                                                                                                                                                                               |
| Confusion, Hubbub and Order scale (CHAOS):                                                                               | Parent report scale specially designed to be administered to parents for assessing chaos in the child's home. A measure of confusion and disorganisation.                                                                                     |

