#### **6.4 Blinding Arrangements**

The project manager, participants and nurses will be aware of the allocation to treatment arm to enable organisation for the mothers to receive the active or control intervention. Research staff responsible for conducting outcome assessments will be blinded to treatment allocation. Families will be asked not to disclose their randomisation status at assessments; however, those that do will be recorded in the study database and this 'unbinding' will be examined as a potential confounding variable in the outcome analyses.

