| Parenting self-efficacy                                              | X          |    |    | X  |     | X  |
| Health service use                                                   |            | X  | X  | X  | X   | X  |
| Health literacy                                                      |            |    | X  |    | X   |    |
| Parenting styles                                                     | X          |    |    | X  |     | X  |
| Child                                                         |            |    |    |    |     |    |
| Mental and general health                                            |            |    |    |    |     | X  |
| General Health                                                       |            | X  | X  | X  | X   | X  |
| Sibling                                                       |            |    |    |    |     |    |

| Study Measure                                           | Time point |    |    |    |     |    |
|---------------------------------------------------------|------------|----|----|----|-----|----|
|                                                         | Enrol      | 6w | 6m | 1y | 18m | 2y |
| Mental health/behaviour                                 | X          |    |    | X  |     | X  |
| Nurse                                            |            |    |    |    |     |    |
| Use and knowledge of evidence-based clinical strategies | X          | X  | X  | X  | X   | X  |
| MONITORING VARIABLES                                    |            |    |    |    |     |    |
| Maternal social capital/sensitive issues                | X          |    |    | X  |     | X  |
| Child birth data                                        |            | X  |    |    |     |    |
| Child growth data (e.g. height & weight)                |            | X  | X  | X  | X   | X  |
| Intervention dose and fidelity                          |            | X  | X  | X  | X   | X  |

Time points: w=week, m=month, y=year. Enrolment will occur within a fortnight of screening at the antenatal hospital clinic. Monitoring items are variables that may be used to describe the sample or to control for potential confounding and are not collected as demographics.

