We acknowledge that our choice of a 40% attrition rate is lower than the attrition in MECOSH (45% participated in 2 year follow-up in the control arm compared with 57% in the intervention arm). This is for two reasons. First, in MECOSH, participants were lost to follow-up if they changed addresses out of the single Sydney suburb that the trial was conducted in. We expect the right@home families to be equally transient, but the nurses and researchers can still reach them if they live in the same region. There is also the possibility that families could swap nurses if they move out of one right@home region and into another, and this will be organised if and when cases arise. As such, we are confident that we will lose fewer families to itinerancy. Second, according to [name], part of the MECOSH attrition was due to families not being high-risk enough to benefit from the program and feeling that they did not need the information. This is supported by the home visiting literature which suggests that the most vulnerable families benefit most from the interventions. For this reason, right@home aims to recruit only the most vulnerable families (i.e. ~5% rather than ~15% in MECOSH).

We acknowledge that differential attrition, as evident in the MECOSH follow-up, is a significant risk. The primary reason for the follow-up phone calls to all families at 6 weeks, 6 and 18 months is to maintain contact. The secondary reason is to collect data so that the burden of the face-to-face assessments is reduced. We will contact the right@home nurses and maternal and child health nurses responsible for the usual care families for contact details when we lose contact. If it is

possible, we will obtain consent to record the family's Centrelink number so that we can obtain current contact details if we lose contact with the family. We are currently making inquiries into whether this is possible and will only be able to do it with the correct authority and ethical approval.

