#### **11.2 Data Storage**

All participants and nurses will be given unique numerical identifiers (an ID code) for use throughout the study. A single, online electronic database will record all participant and nurse details. It will be hosted by the MCRI server, because it is secure and meets ethical confidentiality requirements. Nurses, researchers and managerial staff will have different levels of access to the password-protected database. Nurses will only be able to access the details of the families in their caseload; researchers will be able to access the details of families but not their randomisation status; and managerial staff will be able to access all levels as required. All participant and nurse questionnaire data will be identified by ID code only and be stored in the secure electronic database. Digital video

material (i.e. collected by intervention nurses to conduct video feedback with families) will be attached as electronic files to the family's record in the database. Any written materials will be scanned and also saved with the family's record on the electronic database. Hardcopy (paper) nurse materials will be stored in a locked cabinet at CHETRE, and hardcopy family materials will be stored in a locked cabinet at CCCH. Only project staff directly involved in the analysis of the data will have access to these materials and the electronic database. The database linking the participants' identity to their ID code will be maintained electronically on a password protected file.

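### Questions that supposedly blind researchers must ask invite disclosure of the arm, and nothing separates them from scoring of the observer-rated primary measures

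*Protocol*

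**What the plan says.** **Who is blind.** Section 4.1: "Researchers responsible for collecting the data, but not families or nurses, will be blinded". Section 6.4 repeats this for assessors: "Research staff responsible for conducting outcome assessments will be blinded to treatment allocation". The first statement is the wider one and covers telephone callers as well as home assessors.

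**Safeguards.** Section 6.4: "Families will be asked not to disclose their randomisation status at assessments". Disclosures that occur are recorded and examined as a possible confounder. Section 11.2 denies researchers access to randomisation status. Section 5.2 keeps the nurses' fidelity checklists from assessing researchers. Section 6.5.2 withholds allocation from research staff and the statistician until all 24-month assessments are done.

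**What is asked.** Section 7 has the research team telephone mothers at 6 weeks, 6 months and 18 months. Section 9.1 says that in those calls "women will be asked what things they like and dislike about being part of the study", and that they are also asked about harm. The wording is still to be developed and approved. Table 4 lists "Health service use" at every follow-up, including 1 and 2 years.

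**What is observed.** Tables 2 and 4 place the observational HOME responsivity subscale and the observational home safety audit, both primary measures, at 1 and 2 years.

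**Records and tracing.** Section 11.2 says that digital video "material (i.e. collected by intervention nurses to conduct video feedback with families) will be attached as electronic files to the family's record". Section 10.1 says: "We will contact the right@home nurses and maternal and child health nurses responsible for the usual care families for contact details when we lose contact".

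**The concern.** Intervention mothers are offered at least 25 nurse home visits, a dedicated social care practitioner and groups reserved for their arm (Section 5.1.1). For such a mother, a candid answer about what she likes in the study, or which services she uses, may well identify her arm. The protocol asks her not to disclose and then asks questions that prompt disclosure.

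What is at stake is the scoring of parent responsivity and home safety, which rest on an observer's judgement. If an assessor knows the arm and scores more favourably because of it, the shift falls on one arm and cannot be told apart from a treatment effect. The HOME subscale is the only measure listed for the responsivity outcome.

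**Working it through.** **1. Contacts side by side** (Section 7, Section 9.1, Tables 2 and 4):

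| Contact | Mode | Questions that may disclose the arm | Observer-rated primary measures |
|---|---|---|---|
| 6 weeks | phone | study likes/dislikes, service use | none |
| 6 months | phone | study likes/dislikes, service use | none |
| 1 year | home | service use | HOME responsivity, safety audit |
| 18 months | phone | study likes/dislikes, service use | none |
| 2 years | home | service use | HOME responsivity, safety audit |

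All three calls precede the 2-year primary assessment. At both home visits, service use shares the contact with the observational scoring. No section places the scoring first, gives the disclosing questions to unblinded staff, or keeps callers apart from home assessors.

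**2. Records.** Section 11.2 makes three statements that do not fit together. Researchers may see family details but not allocation. Intervention-only video sits in the family's record. Only staff who analyse the data may reach the materials and the database. The last would shut out the researchers and nurses to whom the same section has just given access. Section 5.2 expressly keeps checklists from assessors; no such sentence covers the video.

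**3. Adjustment for disclosure.** The disclosure flag arises after randomisation and is likely to differ by arm. Its coefficient would mix any shift in scoring with the kind of mother who discloses. It would also miss an assessor who infers the arm without being told. Conditioning on it therefore does not restore an unbiased comparison.

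**4. The protocol's own figure.** Section 10.1 gives 400 per arm, 60% retention, intra-class correlation 0.02, cluster size 29, 80% power and 0.315 SD. It states no alpha; I assume two-sided 0.05.
- Retained per arm: 400 × 0.60 = 240.
- Design effect: 1 + (29 − 1) × 0.02 = 1.56.
- Effective number per arm: 240 / 1.56 = 153.8.
- Standard error: √(2 / 153.8) = 0.114 SD.
- Power at 0.315 SD: Φ(0.315 / 0.114 − 1.96) = 78.9%, close to the stated 80%.

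**5. Illustration only.** Suppose there is no true effect, assessors learn the arm for a share *u* of intervention mothers, and they score those mothers *b* SD too favourably. Neither input is in the protocol. Bias is δ = *u* × *b*, and the false-positive rate is Φ(−1.96 + δ/0.114) + Φ(−1.96 − δ/0.114).

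| *u* | *b* | Bias δ (SD) | δ / 0.315 | False-positive rate |
|---|---|---|---|---|
| 0.5 | 0.1 | 0.05 | 16% | 7.2% |
| 0.5 | 0.2 | 0.10 | 32% | 14.2% |
| 1.0 | 0.2 | 0.20 | 63% | 41.9% |

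This shows why leakage could matter, not how much of it there will be.

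**The case against.** The protocol plainly anticipates leakage and has several safeguards, listed above. Item order within a visit normally belongs in an assessment manual, and the questionnaires are not shown. These are fair points, and several stronger readings that a reader might infer are not supported:

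- **That the questions will reveal the arm.** The like/dislike wording is not final and the service-use items are not shown. Usual-care families also have nurse contact, volunteer visiting and family support (Section 5.1.1), so reporting a nurse visit does not by itself identify the arm. The questions invite disclosure; they do not guarantee it.
- **That the caller scores the home visit.** No section says so. Section 6.6.1 describes the caller as a chief investigator or research officer, while Section 1.2 gives clinical assessments to research assistants. What stands is that the roles are not kept apart, and that Section 4.1 requires callers to be blind in any case.
- **That blind researchers can open the nurse video.** Section 11.2 does not say this. It sets access levels and has a sentence restricting materials to analysis staff. What stands is the inconsistency and the missing express bar.
- **That tracing unblinds assessors.** Section 10.1 does not give tracing to assessors, and the project manager already knows allocation (Section 6.4). Naming that role would settle it.
- **That asking mothers not to tell is the only safeguard.** It is one of several.

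The leak also bears on only part of the primary set. The sleep item, meal diary, CHAOS, language inventory and some HOME subscales are parent-reported, so an assessor's rating shift does not act on them in the same way.

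The objection does not remove the conflict between asking mothers not to disclose and prompting them to, or the lack of anything that protects the observational scores from the answers.

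**Conclusion.** The point holds in limited form. The protocol's procedures invite disclosure of the arm to researchers whom it calls blind, and it does not protect the observer-rated measures from what they may hear. Section 11.2 should also be made consistent. The safeguards reduce the risk, but the planned handling of disclosure in the analysis cannot remove assessor bias once it has occurred.

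The size cannot be estimated: the illustrative bias of 0.05 to 0.20 SD rests wholly on assumed disclosure and scoring shifts. The exposed primary measures are HOME responsivity and the safety audit; height and weight are also collected by observation but leave less room for judgement. Who performs the allocation is a separate matter, and this point does not depend on it. I rate this as an inexpensive improvement worth making, not as evidence that blinding has failed.

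**What to change.** 1. **Home visits (Sections 7 and 8).** At 12 and 24 months, complete and lock on the tablet the observational HOME items, safety audit and height/weight before any service-use, study-experience or adverse-event question.
2. **Telephone calls (Section 9.1).** Ask the like, dislike and harm questions last and hide the answers from whoever does that family's home visits, or have an unblinded role ask them. The wording still has to go to the ethics committee, so this can travel with it.
3. **Records (Section 11.2).** State that nurse video and scanned nurse materials are closed to the researcher access level, and reconcile the sentence restricting access to analysis staff with the access given to researchers and nurses.
4. **Tracing (Section 10.1).** State that tracing through nurses is done by the already-unblinded project manager, who passes on contact details only.

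The cost is a reordering of forms, a database permission and one task assigned to a role that already knows allocation. No added participants or visits are needed. The small downside is that locked observational scores cannot use anything seen late in the visit.
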